## Abstract

Chronic wound management is a global challenge. Millions of patients suffer from nonhealing ulcers and health systems are overwhelmed by the growing demand for treatment. Despite the prevalence of chronic wounds, the emergence of wound centers and specialized physicians is a recent phenomenon. Likewise, clinical research in wound healing is in its infancy. To date, many of the products in wound care have little or no clinical evidence. The field needs standardized clinical trial design, endpoints recognized by clinicians and payers, and improved overall clinical evidence. Wound healing is impeded by the presence of bacterial biofilms, which exist in most chronic wounds. It is not surprising that biofilm disruption is the focus of wound management and essential to the healing process. Multiple laboratory and preclinical studies demonstrate promising efficacy of several antimicrobials in treating biofilms; however, the field lacks in vivo clinical studies. In addition, a standardized trial design to evaluate efficacy of antimicrobials in chronic wounds does not exist. The advent of new diagnostic technologies, such as fluorescence imaging, has led to clinical trial designs that are reliable, easier to conduct, and cost efficient. The protocol presented here describes a randomized controlled double-blind trial designed to evaluate antiseptics in chronic wounds.

## 1. Introduction

Chronic wounds cause patient suffering, challenge clinicians, and stress health systems across the world. A new medical specialty focusing on hard-to-heal wounds has emerged to meet the increasing demand posed by millions of patients with wounds that fail to heal. As with any new field, there is limited evidence supporting the treatment regimens currently in use. In addition, clinical trials in wound healing lack standardization in endpoints and consistency in design. The goal of the wound care community is to increase the level of evidence for treatment modalities, standardize clinical trial design, and develop meaningful endpoints.

Several factors contribute to delayed healing in chronic wounds [1]. Key among them are excessive amounts of bacteria. A recent clinical trial demonstrated that more than 80% of chronic wounds harbor bacterial levels that impede wound healing [2]. Moreover, the bacteria in chronic wounds exist preferentially in a biofilm phenotype [3]. The bacteria in biofilms are resistant to antibiotics and may be protected from topical antiseptics [4]. They delay wound healing and frequently recur [5]. As a result, clinicians have adopted a biofilm-based approach in the treatment of chronic wounds that includes debridement, wound cleansing, and the use of topical antimicrobials [6]. Antiseptic cleansers and topical antimicrobials are supported by preclinical evidence [7], but there are few well powered prospective in vivo clinical trials.

In current practice, the choice of wound cleansers is based on professional experience, clinician preference, or institutional policy [7]. Unfortunately, there is sparse evidence that cleansers and topical antimicrobials reduce biofilm or promote healing in patients with chronic wounds. In order to garner greater evidence for these agents, a randomized controlled double blind clinical trial design is presented.

The efficacy of the treatment regimen in eliminating bacteria and biofilms is achieved using fluorescence imaging (MolecuLight, Toronto, Canada). Fluorescence imaging (FL) is a validated noninvasive point-of-care method for assessing bacterial load in chronic wounds [2]. It detects bacterial levels greater than >104 CFU/g [8] and obviates the need for invasive biopsies. Incorporating fluorescence imaging into the trial design permits rapid and repeatable assessment of bacterial levels throughout the study: This trial will assess bacterial levels weekly. This design would be impractical using tissue cultures that are invasive and expensive.

Described here is the BIAKOS (Sanara, Fort Worth, TX, USA) lower extremity ulcer trial (BLEU): a randomized double-blind controlled trial designed to compare healing rates between standard of care (normal saline wash and an amorphous gel) to the combination of synergistic antimicrobial cleanser and antimicrobial gel in chronic lower extremity ulcers. It is the first major trial on antimicrobials and one of the few double-blind studies to be conducted in the wound care space.

In two biofilm models, different types of commercially available wound cleansers will be compared: BIAKOS, a polyhexamethylene biguanide (PHMB)-based cleanser (PHMB-1), has the largest biofilm reductions when compared to all other studied cleansers after a single application and significant reductions in MRSA and C albicans biofilms following daily treatments over 72 h compared to all other test articles. Results of this preclinical trial demonstrate that a PHMB-based cleanser used daily performed significantly better than other cleansers [9]; however, studies to examine the clinical effectiveness on bacterial load and actual wound outcomes are needed.

Commercially available antimicrobials promote products based on lab or preclinical evidence rather than trials in the wound clinic population. The BIAKOS™Lower Extremity Ulcers trial is a randomized double-blind controlled trial designed to compare healing rates between normal saline wash and amorphous gel to the combination of synergistic antimicrobial cleanser and antimicrobial gel in chronic lower extremity ulcers. It is the first major trial on antimicrobials and one of the few double-blind studies to be conducted in the wound care space.

## 2. Materials and Methods

BLEU is a randomized double-blind controlled clinical trial comparing a synergistic antimicrobial cleanser (AMC) and an antimicrobial gel (AMG) to a normal saline wash and an amorphous gel (NSS-HG) in reducing bioburden and promoting healing in chronic lower extremity ulcers (clinicaltrials.gov #NCT05107050). This study will be conducted at up to five SerenaGroup^®^ Research Foundation centers throughout the United States with up to 60 subjects with acute or chronic non healing wounds participating. The study is anticipated to be completed within one year. The study population will be drawn from patients suffering from chronic wounds who are attending wound clinics or residing in skilled nursing facilities. Section 2.6 details the inclusion and exclusion criteria for the BLEU trial.

### 2.1. Objectives and Endpoints

The primary objective for the BLEU clinical trial is to compare healing rates (percent area reduction, PAR) between normal saline wash and an amorphous gel (NSS-HG) to the combination of a synergistic antimicrobial cleanser (AMC) and an antimicrobial gel (AMG) in chronic lower extremity ulcers, including diabetic foot (DFU) and venous leg ulcers (VLU). The primary endpoint is PAR in 4 weeks, with a goal healing rate of 40% in 4 weeks. There is a large body of evidence that supports this rate of healing for DFUs and VLUs [10], and the FDA-sponsored Wound Care Collaborative Community (WCCC) has recommended it as a surrogate endpoint [11].

In addition, an important endpoint in antiseptic clinical trials is a reduction in bacteria. The use of point-of-care fluorescence imaging has simplified this process. Fluorescence imaging will be obtained at every visit and the reduction in bacterial bioburden will be compared between ulcers treated with NSS-HG and AMC-AMG.

Additional secondary endpoints common to most wound-healing clinical trials will be the difference in pain scores and adverse events between subjects treated with NSS-HG and AMC-AMG.

Exploratory endpoints are encouraged if they do not interfere with the primary or secondary endpoints. They contribute to the body of knowledge on chronic wounds and can improve the conduct of future trials. This study will examine host protease levels (matrixmetaloproteases 8 and 9 and neutrophil elastase) using a point-of-care lateral flow test (WOUNDCHEK PROTEASE TEST, WoundChek, Gargrave, UK). In clinical trials, the diagnostic accurately identified wounds with high levels of inflammation. In wounds with a positive test for elevated protease activity (EPA) only 10% were healed at 12 weeks [12].

### 2.2. Blinding

In the BLEU trial, the subjects and investigators will be blinded to the treatment arm. Subjects will be randomized in 1:1 fashion to either NSS-HG or AMC-AMG. Unblinded staff will prepare the solutions for the two study arms the morning of the day of enrollment. NSS-HG or AMC-AMG will be placed in labeled containers consistent with the randomization scheme. The NSS-HG or AMC-AMG will be applied at randomization and weekly thereafter. The unblinded research staff will provide the subject with a 4-week supply of NSS-HG or AMC-AMG for home use. For this trial, the solutions will be mixed in the clinic for practical reasons. In future trials utilizing this design, the aim is to have the Investigational sites receive the product and control in generic containers identified by numbers.

Given the low risk of the device, the authors do not anticipate breaking the blind during the trial; however, if unblinding is required for a medical emergency the medical monitor will be notified immediately. The subject’s treatment assignment will not be revealed to other blinded staff unless required for safety reasons. The circumstances leading to the unblinding, and date will be fully documented in the subject’s source documentation. The subject will be withdrawn from the trial at the time of unblinding.

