After the screening visit, enrolled patients will start treatment visit 1. At this treatment visit, initial procedures will be conducted:Confirmation of inclusion criteria and randomization to treatment;Photography of the wound and digital surface area measurement;Fluorescence imaging;Wound cleansing with randomly assigned treatment;Post debridement fluorescence imaging;Swab of wound for protease activity;Application of wound dressing at the discretion of the principle investigator;A four-week supply of the assigned treatment is provided to patients;If applicable, wound debridement, measurement, off-loading walker fitting (DFU applicable), or application of multilayer compression (VLU) is conducted.

At the subsequent treatment visits (visits two through four), all steps will be repeated except for step eight. At the end of the study visit (treatment visit five), final assessments will be conducted to review potential adverse events, concomitant medications, clinical signs and symptoms of infection, and pain status. Pain intensity of the reference ulcer will be assessed before and after any wound cleaning. If applicable, wound debridement, measurement, and photography will be performed. The study exit form will be provided to patients and additional placement of standard-of-care dressings will be provided if the wound has not healed.

Subjects will return weekly for 4 weeks after randomization unless the wound heals, the subject withdraws, or the subject is lost to follow-up.

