### 2.8. Statistical Methods

Summary statistics including mean, median, interquartile range, counts, and percentages are used to summarize demographic and treatment data collected from patients.

When determining sample size, a power of 80% is needed to detect a difference between groups of 0.35. With sample sizes of 30 patients per group, 80% power is achieved.

A chi-square test of independence will be conducted to assess endpoints concerning proportions. For the BLEU trial, the chi-square test will be used to assess the primary and secondary endpoint. The primary endpoint is to determine the relationship between the treatment and the patient, reaching a threshold of 40% PAR in four weeks. The secondary endpoint is to determine the relationship between the treatment and a reduction of bacterial load of <10^4^ CFU/g (by Fluorescence) by the fifth treatment visit. The assumptions of the chi-square test of independence must be met. These include randomly selected patients, independent treatment groups, and the use of two categorical frequency variables. The expected frequency for each group must be greater than five. A significance level of 0.05 will be used for this hypothesis test. For the primary endpoint, the null hypothesis states that the proportion is equal for both treatments, whereas the alternative hypothesis states that the proportion is not equal for both treatments. Statistical software such as R (version 4.3.1), Excel (version 365), or a TI-83 calculator (TI-83 Plus Graphing Calculator|Texas Instruments) will be used to calculate the chi-square test statistic and the *p*-value.

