### 2.9. Subject Withdrawal

All subjects have the right to withdraw at any point during treatment without prejudice. Whether each subject completed the clinical study will be documented. If, for any subject, study treatment or observations are discontinued, the reason(s) will be recorded. The investigator can discontinue a subject at any time if it is considered medically necessary. The termination of study participation is not anticipated to affect subject safety. If a subject withdraws consent to participate in the study or is withdrawn by the investigator, attempts must be made to obtain permission to record at least survival data up to the protocol-described end of the subject follow-up period. Reasons for withdrawal or early termination will be obtained whenever possible.

A subject will be considered lost to follow-up if they cannot be contacted after 5 phone calls and 3 letters.

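### Unblinding removes a subject from the trial, and the data floor after withdrawal is survival, so four-week wound area and fluorescence can be lost with no spare subjects planned

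*Protocol article*

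**What the plan says.** Four places in the protocol article decide when observation ends and what is collected afterwards.

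- **Section 2.2 (Blinding).** Breaking the blind is reserved for a medical emergency and is not expected to happen. If it does: "The subject will be withdrawn from the trial at the time of unblinding". The withdrawal is from the trial, not only from study product.
- **Section 2.9 (Subject Withdrawal).** The investigator may discontinue a subject when medically necessary. After withdrawal of consent or withdrawal by the investigator, "attempts must be made to obtain permission to record at least survival data", up to the end of the planned follow-up period.
- **Section 2.7 (Study Procedures).** "Subjects will return weekly for 4 weeks after randomization unless the wound heals", or the subject withdraws or is lost. Early termination for any reason calls for an exit form, and for dressings if the ulcer is not healed. That sentence names no wound measurement or image.
- **Section 2.8 (Statistical Methods).** The primary endpoint is reaching 40% percent area reduction (PAR) in four weeks. The bacterial endpoint is judged by fluorescence by the fifth treatment visit.

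Table 1 schedules wound measurement, fluorescence, pain and the protease test at TV5, Day 28.

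On size, Section 2 allows "up to 60 subjects with acute or chronic non healing wounds participating", and Section 2.8 states: "With sample sizes of 30 patients per group, 80% power is achieved".

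**The concern.** A medical emergency or a medically necessary discontinuation happens after randomisation and may be related to the assigned treatment or to how the wound is doing. If the subject then leaves the trial, the four-week wound area may never be measured. Section 2.9 already intends contact, with permission, to the end of follow-up, but the one item it insists on is survival, which is not an endpoint anywhere in the article.

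This is a fault in stated rules for data collection, not a gap left to an analysis plan. An analysis plan can say how a missing Day 28 value is handled; it cannot supply the measurement. In a trial of this size, a few outcomes lost unevenly between arms would weaken the randomised comparison.

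Ending visits at healing is a separate and lesser matter. It leaves the primary result known at the time of closure, but reopening before Day 28 and the TV5 assessments would not be seen.

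**Working it through.** **Inputs.** From Section 2.8: significance level 0.05 ("A significance level of 0.05 will be used for this hypothesis test"); a two-sided test, since "the alternative hypothesis states that the proportion is not equal for both treatments"; and "a power of 80% is needed to detect a difference between groups of 0.35", with 30 per group. From Section 2: at most 60 subjects. Allocation is 1:1. No group response rates and no dropout rate are stated, so the control rate p1 is an assumption, ranged from 0.05 to 0.60, with p2 = p1 + 0.35.

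**1. The plan's own figure.** With p̄ = (p1 + p2)/2,

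power = Φ{ [0.35·√n − 1.96·√(2p̄(1−p̄))] / √(p1(1−p1) + p2(1−p2)) }.

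At n = 30 and the least favourable rates, 0.325 v 0.675: (0.35 × 5.477 − 1.96 × 0.7071)/0.6624 = (1.917 − 1.386)/0.6624 = 0.802, so power is 0.789. Over the whole range of control rates, power runs from 0.789 to 0.922. The stated 80% is reproduced; it is not at issue.

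**2. Allowance for loss.** 60 − 2 × 30 = 0. All 60 subjects must supply a four-week outcome for the stated power to apply.

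**3. Weight of one subject.** 1/30 = 3.3 percentage points of an arm's response rate.

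**4. Bounds with k unknown outcomes per arm.** Let a and c be the known responders on the active and control arms.

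- Lowest possible difference: (a − c − k)/30.
- Highest possible difference: (a + k − c)/30.
- Width: 2k/30.

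| k per arm | Width of the bounds |
|---|---|
| 1 | 0.067 |
| 2 | 0.133 |
| 3 | 0.200 |

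The design difference is 0.35. The values of k are illustrations; the documents give none.

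**5. Power if outcomes are lost at random.** Same formula, rates 0.325 v 0.675:

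| Evaluable per group | Power |
|---|---|
| 30 | 0.789 |
| 28 | 0.759 |
| 27 | 0.743 |
| 25 | 0.709 |

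Keeping 30 evaluable would need 30/0.95, 30/0.90 or 30/0.85 per group, which round up to 32, 34 or 36, at an assumed loss of 5%, 10% or 15%.

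**6. Healing before Day 28.** A closed wound has 100% PAR, and 100% exceeds 40%, so the subject is a known responder when closure is recorded. How such subjects are scored still matters. Assume, for illustration only, true rates of 0.325 v 0.675 with early healing in 5% of controls and 15% of the active arm:

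- Scored as responders: the difference stays 0.35.
- Dropped: (0.325 − 0.05)/0.95 = 0.289 and (0.675 − 0.15)/0.85 = 0.618; difference 0.328, power 0.69.
- Scored as failures: 0.275 v 0.525; difference 0.25, power 0.51.

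The article does not say that healed subjects are dropped or failed. The last two lines show only why the scoring should be put in words.

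**The case against.** The case on the other side is substantial.

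- **Unblinding should be rare.** Section 2.2 limits it to emergencies and expects none, and Section 2.11 calls treatment-related adverse events unlikely. This stands: the effect by that route is probably small. Investigator discontinuation in Section 2.9 carries no similar expectation.
- **Survival is a floor.** A reader might infer that only survival is sought after withdrawal. The text does not say so: it sets a minimum and forbids nothing more. It also depends on permission, rightly so where consent has been withdrawn. What remains is that no endpoint variable is in the minimum.
- **Healing does not lose the primary outcome.** A reader might infer that stopping visits at healing removes the best outcomes from the Day 28 data, and build examples in which deleting healed responders from the active arm overturns a significant result. Such examples need an analysis restricted to subjects seen at TV5, which the article nowhere defines, and they place every deletion in one arm. Wound area is recorded at every visit, so closure is documented. Fluorescence is also taken at every visit, and its endpoint is judged by the fifth visit, so earlier readings exist.
- **Table 1 may cover early exit.** Its last column joins TV5 with end of study and includes wound measurement and imaging. But that column is dated Day 28, and the early-termination sentence in Section 2.7 names only the form and dressings. The full protocol may be clearer.
- **Analysis sets and missing-data rules belong to the analysis plan.** Agreed; none is asked for here. Counting every unobserved Day 28 outcome as a failure would be a poor remedy in any case, since it would fail a subject with a documented closed wound who missed TV5.

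**Conclusion.** The point holds as a matter of data collection. Withdrawal from the trial on unblinding, together with a post-withdrawal minimum that names a non-endpoint, allows four-week wound area and fluorescence to be lost for reasons that may be related to treatment or wound course. The planned number leaves no slack.

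The size is unknown. It is probably small for unblinding and unquantified for investigator discontinuation. Each subject lost is 3.3 points of an arm's rate, and three unknown outcomes per arm, an assumed figure, would leave bounds 20 points wide against a design difference of 35.

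The documents do not support a claim that the stated power is wrong, that healing makes the primary outcome missing, or that the trial's result would be overturned. For healed subjects, what goes unobserved is reopening before Day 28 and the TV5 fluorescence, pain and protease data.

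**What to change.** 1. **Section 2.2.** Separate stopping study product from leaving the trial. An unblinded or discontinued subject stays in follow-up to Day 28 unless consent is withdrawn. Whether product continues remains a clinical decision.
2. **Section 2.9.** Replace the survival minimum with at least wound area, photograph and fluorescence image at Day 28 or, failing that and with permission, at early exit. Name the same items in the early-termination sentence of Section 2.7.
3. **Section 2.7.** Keep the TV5 visit for subjects whose wound has healed, to confirm closure. State that documented closure counts as reaching 40% PAR unless reopening is observed.

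**Cost.** A few wording changes and some additional TV5 visits. These fall within the five-visit schedule and the USD 35 per-visit payment in Section 2.10. The sample size does not change. The change has to come before the affected subjects pass Day 28, because the measurements cannot be recovered later.

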### 2.3. Diagnosis

One of the challenges in conducting clinical trials in wound healing is ensuring that the wound type under study has been appropriately diagnosed. The clinical trial described here examines two ulcer types: diabetic foot (DFU) and venous leg ulcerations (VLU). The diagnosis of these two wounds is primarily clinical. DFUs occur on the plantar aspect of the foot in diabetic patients with sensory neuropathy. An objective assessment of vascular status using the ankle brachial index (ABI), the toe brachial index (TBI), or another screening test will rule out patients with significant ischemia. Venous leg ulcers develop on the medial or lateral gaiter regions of the lower extremities. Most clinical trials enroll VLU patients based on clinical signs and symptoms: lower extremity edema, hyperpigmentation of the skin, loss of hair, atrophy blanch, thickening of the nails, and lip dermatosclerosis. The venous ulcer is shallow with an irregular border. For ulcers that exhibit these signs, the diagnosis is straightforward. For ulcers suspected to be VLUs but that do not have the characteristic appearance, the investigator should consider biopsy to rule out vasculitis, cancer, or other pathology. The investigator may also wish to obtain a venous duplex scan to demonstrate venous insufficiency. In the past, VLU clinical trials mandated venous duplex procedures; however, this adds considerable cost to the trial without adding significant benefit.

